#### Inclusion criteria

2.3.2

(1)Diagnosed with coronary heart disease;(2)Left ventricular ejection fractions (LVEF) ≤50%;(3)New York Heart Association (NYHA) classification II∼IV;(4)Standardized western medicine therapy for IHF currently in a stable condition;(5)Signed informed consent.

#### Exclusion criteria

2.3.3

(1)Acute HF;(2)Acute coronary syndrome;(3)Preparation for revascularization therapy or heart transplantation;(4)Already received or preparing to receive cardiac resynchronization therapy (CRT)/implantation of cardiac pacemaker;(5)Special treatments should be used for patients with comorbidities such as severe liver or renal failure and malignant tumor which could influence the clinical treatment of IHF;(6)Pregnant or breastfeeding women, or women at childbearing age without reliable methods of contraception;(7)Participated in other studies within 2 months;(8)Suspected or definite allergy to intervention drugs.

### Sample size

2.4

According to a previous study,^[17]^ we assume that the rate of cardiac function improvement is 22% of patients in QSYQ group and 15% in control group. The sample size is same in 2 groups. A total sample size of 1200 patients should be recruited with a power of 0.8, a 2-sided alpha of 0.05 and a dropout rate of 20% by PASS 2011 software.

### Intervention

2.5

The patients will be divided into 2 cohorts: exposure group and non-exposed group according to whether are taking QSYQ in real clinical practice. Patients receive treatments from researchers of QSYQ or not as they would in the real world, and if they have no preference, the decision for group will be made by researchers according to their professional experience. Patients in the non-exposed group will receive standardized western medication according to patient's clinical conditions, which includes antiplatelet agents, statins, diuretics, angiotensin-converting enzyme inhibitor or angiotensin-receptor blocker, β-blockers, aldosterone receptor antagonist, digoxin, vasodilating agents, and so forth according to HF and chronic stable angina guidelines.^[15,16]^ Patients in the exposure group will be given 1 packet (0.52 g) of QSYQ thrice daily 3 months besides standardized western medication. In both groups, any other Tradiational Chinese Medicine (TCM) drug will be prohibited. Western medicine will be administrated for the comorbidities (such as hypertension or diabetes) and complications according to the relevant guidelines. All drugs will be recorded in case report form.

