### Statistical analysis

2.9

Statistical analysis will be performed by the Clinical Trials Center of First Teaching Hospital of Tianjin University of TCM based on intention-to-treat principle. The continuous variables will be expressed as the mean with standard deviation and tested by *t* tests or Wilcoxon rank sum test. Categorical variables will be expressed as percentages and tested by chi-squared test or Fisher exact test. Survival analysis will be conducted by the log-rank test and Cox regression model. Statistical analysis on the missing data will be adjusted by an estimating equation or statistical model in the final analysis. The statistical significance is defined as *P* <.05. Data analysis will be conducted by Statistical Analysis System (SAS) software version 9.3 (SAS Institute Inc., Cary, NC).

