## Discussion

3

In China, QSYQ plus western medicine is widely used for patients with IHF, especially for those who are dissatisfied with the efficacy or want to relieve the side effects from western medication. Current evidences on QSYQ for IHF mainly come from RCTs with poor methodological quality.^[13]^ The external authenticity is limited when patients have preferences for treatments in RCT design.^[14]^ In this context, we design a multicenter, prospective, observational cohort study considering the patients’ preference in the real clinical practice. It will provide new evidence on QSYQ for IHF in real clinical practice.

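### Exposure is defined by current use of QSYQ while the text also describes a choice at enrolment, and no criterion addresses earlier use, so continuing users can be mixed with starters

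*Protocol article*

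**What the plan says.** The Intervention section (2.5) of the protocol article describes exposure in two ways.

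- **By current use.** Patients are divided into "exposure group and non-exposed group according to whether are taking QSYQ in real clinical practice".
- **By a decision and supply at enrolment.** "Patients in the exposure group will be given 1 packet (0.52 g) of QSYQ thrice daily 3 months besides standardized western medication". For undecided patients, "if they have no preference, the decision for group will be made by researchers according to their professional experience".

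The eligibility lists are numbered, with five inclusion and eight exclusion criteria. None mentions QSYQ or other TCM use before enrolment. The criterion on background treatment concerns western medicine only: "Standardized western medicine therapy for IHF currently in a stable condition". The exclusions that look back in time concern cardiac devices and research participation ("Participated in other studies within 2 months"), not herbal treatment. Section 2.5 restricts other herbal drugs during the study: "In both groups, any other Tradiational Chinese Medicine (TCM) drug will be prohibited". No wash-out is stated for QSYQ or for those drugs.

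The Discussion says that "QSYQ plus western medicine is widely used for patients with IHF", and the Background dates the product's approval to 2003. NYHA class and MLHFQ are first measured at V0, then at 1 and 3 months. The sample size rests on a rate of cardiac function improvement. The analysis is "based on intention-to-treat principle".

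**The concern.** If grouping follows current use, the exposed cohort can contain two kinds of patient: those who start QSYQ at V0 and those who were already taking it. For a starter, change after V0 includes the effect of starting. For a continuer, V0 is already an on-treatment value, so any benefit gained earlier cannot count as improvement. Continuers have also tolerated the product long enough to remain on it, so adverse events that occur soon after starting lie outside their observation period. Safety is one of the study's two stated aims.

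The non-exposed group has a matching problem. It can contain patients who stopped QSYQ shortly before V0, or who stop another TCM drug because the study prohibits it. Their course after V0 may reflect carry-over or withdrawal rather than western medication alone.

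A mixed comparison answers neither the question about starting QSYQ nor the question about continuing it. The share of each kind of patient would also be unknown unless prior use is recorded.

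**Working it through.** **Does the text close the gap?**

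| Place | What it settles | What it leaves open |
|---|---|---|
| 2.5, grouping sentence | Group follows whether QSYQ is being taken | When it was started |
| 2.5, supply sentence | QSYQ for 3 months in the study | Whether this is first use |
| 2.5, researcher decision | Undecided patients are allocated at enrolment | Patients who already have a preference, including current users |
| Inclusion criteria (5) | Stable western therapy | QSYQ or TCM history |
| Exclusion criteria (8) | Devices, other studies, allergy and others | QSYQ or TCM history |
| 2.5, prohibition | Other TCM drugs during the study | Use before V0; wash-out |

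Nothing in these places keeps an existing user out of the exposed group or a recent stopper out of the non-exposed group. Because grouping is mainly by patient preference, a satisfied current user would be expected to choose QSYQ.

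**The plan's own sample size.** Inputs from section 2.4: 22% versus 15% improved, equal groups, two-sided alpha 0.05, power 0.80, dropout 20%.

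- Unpooled formula: n = (1.960 + 0.842)² × (0.22 × 0.78 + 0.15 × 0.85) / 0.07² = 7.85 × 0.2991 / 0.0049, which rounds up to 480 per group.
- Dropout: 480 / 0.8 = 600 per group, 1200 in total. The stated figure is reproduced.
- The pooled formula gives 482 per group, 603 after dropout and 1206 in total, which is practically the same.

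**Illustration of dilution.** Two assumptions are added that are not in the documents: a share q of the exposed group are existing users, and these improve after V0 at the control rate of 15%. The exposed rate is then

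p₁ = 0.15 + 0.07 × (1 − q).

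With n = 480 evaluable per group, p₂ = 0.15 and p̄ = (p₁ + p₂)/2,

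power = Φ{ [√n (p₁ − p₂) − 1.96 √(2p̄(1 − p̄))] / √(p₁(1 − p₁) + p₂(1 − p₂)) }.

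For q = 20%, p₁ = 0.206 and p̄ = 0.178. The numerator is 21.909 × 0.056 − 1.96 × 0.541 = 0.167, the denominator is 0.5395, and Φ(0.309) = 0.62.

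| q | Exposed rate | Difference (points) | Power | Total N for 80% power, with dropout |
|---|---|---|---|---|
| 0 | 22.0% | 7.0 | 0.80 | 1206 |
| 10% | 21.3% | 6.3 | 0.72 | 1468 |
| 20% | 20.6% | 5.6 | 0.62 | 1830 |
| 30% | 19.9% | 4.9 | 0.52 | 2354 |
| 50% | 18.5% | 3.5 | 0.31 | 4466 |

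The last column uses the pooled formula, hence 1206 rather than 1200 in the first row.

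**Direction.** The table shows one mechanism only, a treated baseline that pulls the difference toward zero. Two others can act the other way. Continuers are selected for tolerance and perceived benefit, which could favour the exposed group. Withdrawal of other TCM drugs could make non-exposed patients worse; the prohibition covers both groups, but only the exposed have QSYQ in their place. The documents give nothing from which to weigh these mechanisms.

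**The case against.** The strongest reply is that the current-use reading hangs on one awkwardly worded clause. Most of the surrounding text describes a choice made at enrolment: groups follow patient preference, researchers decide for the undecided, and QSYQ is then supplied for 3 months. This stands in part. It makes it likely that many exposed patients are starters. It does not say that all are, and the clause that defines the cohorts says otherwise.

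A second reply is that section 2.5 has all drugs recorded on the case report form, and that the visit table, the flow diagram and the full protocol are not shown. That is fair on medication history, which may well be collected. But the sentence does not say that use before V0 is covered, recording alone does not define the comparison, and the conflicting exposure wording and the numbered eligibility lists are stated here.

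A third reply is that a real-world study should not turn away existing users. This stands against compulsory exclusion. It does not stand against separating them in the analysis.

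Four stronger readings are tempting and are not supported:

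- **Existing users do enter.** The text permits it; nowhere does it say that any participant is one.
- **Efficacy is biased toward no effect.** The mechanisms above pull in different directions.
- **The study is underpowered or its N is wrong.** The 1200 follows from its own inputs, and the power losses depend on an assumed q and an assumed 15% improvement among continuers.
- **Intention-to-treat cannot be applied.** Assessments run from enrolment, so a start is implied; it is not tied to the exposure definition.

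**Conclusion.** The point holds as a design weakness that should be corrected. As written, the exposure rule and the eligibility lists allow starters and continuers of QSYQ into one exposed group, and recent stoppers of QSYQ or other TCM drugs into the other, in a comparison sized on a rate of improvement. For existing users, change from V0 does not measure the effect of starting, and early adverse events go unseen. That much follows from the documents, together with the described wide use of the product.

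The size cannot be derived from the documents. Under the two stated assumptions, power would be about 0.72 with 10% existing users and 0.31 with 50%. This shows that even a modest share could matter; it does not predict what will happen. The argument about improvement applies most directly to cardiac function, for which the sample size section uses an improvement rate. The article does not say whether MLHFQ is analysed as change from V0.

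**What to change.** 1. Reconcile the two descriptions of exposure in section 2.5, so that it is clear whether the exposed group means patients starting QSYQ at V0 or anyone taking it.
2. State that the group is fixed at V0 and that the intention-to-treat analysis keeps patients in that group.
3. Record use of QSYQ and other TCM drugs before V0 on the case report form, over a look-back window set by the clinical team.
4. Make patients starting QSYQ at V0 versus patients not taking it at V0 the primary comparison. Keep prior users as a separate stratum or a sensitivity analysis; excluding them is an option, not a necessity.

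The cost is one additional item on the case report form, a few sentences in the protocol and analysis plan, and fewer patients in the primary comparison. Once the recorded share of prior users is known, the sponsor can judge whether 1200 still leaves enough starters.

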### Outcome measures

2.6

#### Primary outcomes

2.6.1

The primary outcomes include NYHA cardiac functional classification and Minnesota Living with Heart Failure Questionnaire (MLHFQ). They will be assessed at screening (V0 phase), 1 Month ± 7 days (V1 phase), and 3 Month ± 7 days (V2 phase).

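### Two primary outcomes share an unadjusted P < .05, while N = 1200 spends the whole two-sided 0.05 on a single binary rate

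*Protocol article*

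**What the plan says.** Three sections of the protocol article bear on this.

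- **Primary outcomes (2.6.1):** "The primary outcomes include NYHA cardiac functional classification and Minnesota Living with Heart Failure Questionnaire (MLHFQ"). The Abstract names the same two. On timing: "They will be assessed at screening (V0 phase), 1 Month ± 7 days (V1 phase), and 3 Month ± 7 days (V2 phase").
- **Statistical analysis (2.9):** "The statistical significance is defined as" P < .05. This is one threshold for all analyses, with no separate provision for the primary outcomes. The group comparisons named are t or Wilcoxon tests for continuous variables and chi-squared or Fisher tests for categorical ones.
- **Sample size (2.4):** "we assume that the rate of cardiac function improvement is 22% of patients in QSYQ group and 15% in control group". Then: "The sample size is same in 2 groups", and "A total sample size of 1200 patients should be recruited with a power of 0.8, a 2-sided alpha of 0.05 and a dropout rate of" (the dropout figure is 20%). MLHFQ does not enter the calculation.

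**The concern.** The design alpha covers one comparison, but the primary family has two members. Under the threshold as stated, a significant result on either NYHA class or MLHFQ could be reported as a positive primary finding. Two chances at 0.05 give an overall error above 0.05, and the planned power of 0.8 describes only one of the two tests. The choice of rule also bears on N: splitting alpha between the outcomes would need more patients than the 1200 planned, whereas ordering the outcomes would not.

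**Working it through.** **Inputs from section 2.4:** rates 0.22 and 0.15, equal groups, two-sided alpha 0.05 (z = 1.960), power 0.8 (z = 0.842), dropout 20%. **From 2.6.1:** two primary outcomes. **From 2.9:** threshold 0.05. **Assumed, because the article gives none:** the correlation between the test statistics.

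**Step 1. Reproduce N = 1200.** With unpooled variance,

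n per group = (1.960 + 0.842)² × (0.22 × 0.78 + 0.15 × 0.85) / 0.07² = 7.849 × 0.2991 / 0.0049 = 479.1, rounded up to 480.

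Dropout: 480 / 0.8 = 600 per group, 1200 in total. The arcsine formula also gives 480 and 1200. The pooled-variance formula gives 482 per group, hence 603 and 1206. A one-sided calculation gives 950 and does not match. The stated N therefore corresponds to one comparison that takes the whole two-sided 0.05.

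**Step 2. Error if either outcome suffices, one visit.**

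Independent tests: 1 − 0.95² = 9.75%. The bound under any dependence is 2 × 0.05 = 10%.

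Correlated tests (simulated bivariate normal statistics, both-sided rejection beyond 1.96):

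| Assumed correlation | At least one false positive |
|---|---|
| 0.3 | 9.5% |
| 0.5 | 9.1% |
| 0.7 | 8.3% |
| 0.9 | 7.0% |

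**Step 3. Error if both outcomes are required at one visit.** A joint win cannot be more frequent than a win on either test alone, so the error is at most 5% with no split of alpha. For the same reason, joint power cannot exceed the power of either test. It is therefore at most about 0.80, and its actual value is unknown because MLHFQ was never powered.

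**Step 4. Cost of splitting alpha equally (0.025 each).** With 480 evaluable per group, power for 22% against 15% is

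Φ[(0.07 × √480 − z × √(2 × 0.185 × 0.815)) / √0.2991].

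- z = 1.960: Φ(0.836) = 0.798
- z = 2.241: Φ(0.554) = 0.710

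Restoring power 0.8 at 0.025 takes 584 per group (pooled formula), and 584 / 0.8 = 730, or 1460 in total.

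**Step 5. Conditional case: both follow-up visits also tested separately.** Four independent tests give 1 − 0.95⁴ = 18.5%. At common assumed correlations of 0.3, 0.5 and 0.7 the figure is about 17.4%, 15.6% and 13.1%. The article does not state that such testing is planned.

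**The case against.** Several points on the other side have force.

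- **Four tests.** A reader might infer that both outcomes will be tested at both month 1 and month 3, with an error of up to 18.5%. The article does not support this. Section 2.6.1 says when the outcomes are assessed, which is a visit schedule. A single month-3 comparison or a repeated-measures analysis is not excluded. The figures in Step 5 are a conditional scenario only.
- **A broken 5% guarantee.** A reader might also infer that the article claims a 5% error across its primary outcomes and fails to deliver it. No such claim is made: 0.05 appears only as the sample-size alpha and as the significance threshold.
- **Either or both.** The inflation depends on an either-outcome reading. Step 3 shows that requiring both would remove it. This stands, but the article does not state that rule and did not plan power for it.
- **Left to other documents.** The success rule and primary visit are often set out in a full protocol or analysis plan, and neither is shown. Their absence alone would not be a finding. What remains is what the article does fix: two primaries, one threshold, and an N that uses the whole alpha on one rate. These do not fit together under the either-outcome reading that the text permits.
- **Observational design.** Sections 2.1 and 2.5 allocate mainly by patient preference, so nominal error rates hold only without confounding. That is a fair caveat on every rate above. It does not remove the multiplicity question.

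**Conclusion.** The point holds in a limited form. Two primary outcomes are tested against one unadjusted 0.05, and the sample size supports a single comparison at that level. If success on either outcome counts, the chance of at least one false positive is 9.75% under independence and about 8.3% to 9.5% at correlations of 0.7 to 0.3. The correlations are assumptions, and the rates presuppose no confounding. Under a both-required rule at one visit there would be no inflation, but power would be unplanned. This should be settled before any outcome data are compared. It does not invalidate the design or the planned N.

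**What to change.** Make the outcome on which the sample size is built the single primary endpoint, at one named visit, tested at two-sided 0.05. This appears to be improvement in NYHA class, with month 3 (V2) as the natural visit because it ends the three-month study period. The sponsor should confirm both, since section 2.4 names neither the NYHA scale nor a visit.

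Test MLHFQ at the same visit next in a fixed sequence, only if the first test is significant. Label the month-1 comparisons as supportive.

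This holds the error across the two outcomes at 5% (given valid individual tests), keeps N = 1200 and alpha 0.05, and leaves the planned power of the first test intact. It costs only wording. The downside is that MLHFQ alone can no longer carry the primary claim. If the sponsor does not accept that, the alternatives are to require both outcomes, with joint power then worked out, or to split alpha, which takes about 1460 patients to hold power 0.8 for the 22% against 15% comparison.

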#### Secondary outcomes

2.6.2

(1)Composite outcome, including all-cause mortality, frequency of re-admission or emergency due to cardiovascular events (exacerbated HF, acute coronary syndrome, malignant arrhythmias, cardiac shock, coronary revascularization, stroke, pulmonary embolism, peripheral vascular events, etc.) recorded in V1 and V2.(2)LVEF estimated by Simpson's method and cardiothoracic ratio will be assessed at V0 and V2.(3)Symptoms and signs from the 4 TCM diagnostic methods will be measured at V0, V1, and V2.

The entire study period for each patient will be 3 months. All the visits and items are presented in Table 1.

**Table 1 T1:**
[figure not shown]
Time schedule of participant enrollment and follow-up.

### Safety outcomes

2.7

Vital signs, some laboratory tests and adverse events are considered as safety outcomes. Vital signs, which including blood pressure and heart rate, will be measured at V0 and V2. Routine laboratory tests (routine urinalysis, hepatic and renal function and serum electrolyte profile) and electrocardiograms will be measured at V0 and V2. The adverse events will be documented at each visit. The prognosis of adverse events would be observed until the adverse reactions disappear or relieve.

### Data collection

2.8

All data will be documented in the case report form. At the end of the study, the researchers, data managers, and statisticians will review and confirm the database for the final statistical analysis.

### Statistical analysis

2.9

Statistical analysis will be performed by the Clinical Trials Center of First Teaching Hospital of Tianjin University of TCM based on intention-to-treat principle. The continuous variables will be expressed as the mean with standard deviation and tested by *t* tests or Wilcoxon rank sum test. Categorical variables will be expressed as percentages and tested by chi-squared test or Fisher exact test. Survival analysis will be conducted by the log-rank test and Cox regression model. Statistical analysis on the missing data will be adjusted by an estimating equation or statistical model in the final analysis. The statistical significance is defined as *P* <.05. Data analysis will be conducted by Statistical Analysis System (SAS) software version 9.3 (SAS Institute Inc., Cary, NC).

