### Study design

2.1

It is a multicenter, prospective, observational cohort study. A total of 1200 outpatients with IHF from 84 hospitals will in different regions of China are divided into 2 cohorts: exposure group (patients with QSYQ treatment) and non-exposed group (patients without QSYQ treatment). The choice for groups will be mainly made according to patients’ preference. Assessments will be performed at baseline, 1 and 3 months after enrollment. Outcome assessors and statisticians responsible for the final analysis will be blinded. The details of the flow diagram are shown in Figure 1.

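### Groups form by patient or researcher choice, but the only stated analyses that fit the two primary outcomes are unadjusted two-sample tests, so a QSYQ effect cannot be separated from baseline differences

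*Protocol article*

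**What the plan says.** Section 2.1 (Study design) states: "It is a multicenter, prospective, observational cohort study". On group formation it says: "The choice for groups will be mainly made according to patients’ preference". Section 2.5 (Intervention) adds that "if they have no preference, the decision for group will be made by researchers according to their professional experience". Nothing is randomised.

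Section 2.6.1 names two primary outcomes, NYHA class and MLHFQ, measured at screening, 1 month and 3 months.

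Section 2.9 (Statistical analysis) gives the comparisons. "The continuous variables will be expressed as the mean with standard deviation and tested by" t tests or the Wilcoxon rank sum test. "Categorical variables will be expressed as percentages and tested by chi-squared test or Fisher exact test". For time-to-event data, "Survival analysis will be conducted by the log-rank test and Cox regression model", with no covariates named. An estimating equation or statistical model is mentioned, but only for missing data. The analysis is described as intention-to-treat.

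The Discussion says that QSYQ is widely used in China, "especially for those who are dissatisfied with the efficacy or want to relieve the side effects from western medication".

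**The concern.** The aim in the Background is to assess effectiveness and safety, which is a causal comparison. An unadjusted two-sample test answers that question only if the groups would have had the same outcome distribution without QSYQ. Neither route into the groups secures this, because a patient's preference and a researcher's experience can both depend on prognosis.

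The Discussion makes such dependence plausible. It links QSYQ use in general to poor response to western medication or to side effects from it, and both could bear on NYHA class and MLHFQ.

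At stake is the meaning of both primary p-values. A significant difference could reflect QSYQ, the mix of patients who chose it, or both, and a true effect could be masked in the same way. A larger sample does not help, since bias does not shrink as the sample grows.

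**Working it through.** **1. Which stated method applies to which outcome (section 2.9)**

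| Method | Stated use | Fits NYHA or MLHFQ? | Covariates? |
|---|---|---|---|
| t test / Wilcoxon | continuous variables | yes (MLHFQ) | none |
| chi-squared / Fisher | categorical variables | yes (NYHA) | none |
| log-rank / Cox | survival analysis | no | none named |
| estimating equation or model | missing data | not as an adjusted group comparison | none named |

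The document names no propensity score, matching, stratification, centre term or baseline adjustment.

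**2. The plan's own sample size**

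Inputs from section 2.4: 22% vs 15% improving, two-sided alpha 0.05, power 0.80, equal groups, 20% dropout.

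Unpooled formula: n = (1.960 + 0.842)² × (0.22×0.78 + 0.15×0.85) / 0.07² = 7.849 × 0.2991 / 0.0049 = 479.1, so 480 per group. Dividing by 0.8 gives 600 per group and 1200 in total, as stated. The pooled-variance formula gives 482 per group and 1206 in total.

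The sample size is therefore arithmetically right, and it is the size for an unadjusted comparison of two proportions.

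**3. How a baseline imbalance would act**

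The documents give no baseline imbalance, so every input here is assumed. QSYQ has no effect, 25% of NYHA III-IV patients and 10% of class II patients improve, and 480 patients per group are evaluable.

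With 60% of exposed and 40% of non-exposed patients in class III-IV:
- Exposed: 0.60×0.25 + 0.40×0.10 = 0.190
- Non-exposed: 0.40×0.25 + 0.60×0.10 = 0.160
- Spurious difference: 3.0 points, or 3/7 = 43% of the planned 7-point effect

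Rejection probability of the pooled two-proportion test:
- Mean rate 0.175; null SE = √(2×0.175×0.825/480) = 0.02453; actual SE = √((0.19×0.81 + 0.16×0.84)/480) = 0.02451
- Upper tail: 1 − Φ((1.96×0.02453 − 0.03)/0.02451) = 1 − Φ(0.737) = 0.230
- The lower tail adds about 0.001, for a total of 0.231 against a nominal 0.05

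The same calculation for other splits:

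| Class III-IV, exposed vs non-exposed | Crude rates | Difference | Rejection, two-sided |
|---|---|---|---|
| 55% vs 45% | 18.25% vs 16.75% | 1.5 points | 0.094 |
| 60% vs 40% | 19.0% vs 16.0% | 3.0 points | 0.231 |
| 65% vs 35% | 19.75% vs 15.25% | 4.5 points | 0.450 |

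Reversing the splits reverses the sign of the bias.

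**4. Precision cost of adjusting**

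Let R² be the share of exposure explained by covariates (assumed), with variance inflated by 1/(1 − R²). The effective group size is 480 × (1 − R²).

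| R² | Effective n per group | Power for 22% vs 15% | Total N for 0.80 power |
|---|---|---|---|
| 0 | 480 | 0.80 | 1206 |
| 0.10 | 432 | 0.756 | 1340 |
| 0.20 | 384 | 0.705 | 1508 |
| 0.30 | 336 | 0.647 | 1724 |

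The last column uses the pooled 482 per group, divided by (1 − R²) and then by 0.8, rounding up at each step.

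**The case against.** The strongest defence is that this is a condensed article, and that covariate lists and propensity models commonly sit in a fuller plan. Section 2.9 is also generic. It assigns tests to types of variable, could be describing baseline tables as well as outcomes, and never says outright that chi-squared is the primary analysis of NYHA class. This limits what can be claimed: the document does not show that the study will in the end be analysed without adjustment. It does not remove the point. Section 2.9 does state an analysis, and an adjusted primary analysis would replace the stated tests rather than add detail to them.

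The other defences are weaker. Cox regression can carry covariates, but it is tied to survival analysis. The estimating equation is tied to missing data. Blinding of assessors and statisticians protects measurement and analysis, not the make-up of the groups. Intention-to-treat preserves a comparability that only randomisation creates.

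A reader might also infer three stronger things that the documents do not support:
- *That the QSYQ effect is in fact confounded, in QSYQ's favour.* No baseline data are given, and the bias could run either way or be small.
- *That this study's exposed patients are the dissatisfied ones.* The Discussion describes QSYQ users in China generally, which supports plausibility only.
- *That exposed patients enter at a bad point and improve by regression to the mean.* Section 2.3.2 requires a stable condition on standardised therapy, and section 2.3.3 excludes acute heart failure and acute coronary syndrome.

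**Conclusion.** The point stands as a badly chosen stated method. With groups formed by choice and only unadjusted tests stated that fit NYHA class and MLHFQ, the primary comparisons are open to confounding, and their p-values do not test the stated aim.

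The actual bias cannot be sized from the document. False-rejection rates of about 9% to 45% follow from assumed improvement rates and assumed imbalances. They show that moderate imbalance is enough to matter and are not an estimate for this study. The sample size of 1200 is not in error; it is correct for the unadjusted test.

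**What to change.** Make the primary analysis of both outcomes a prespecified covariate-adjusted or propensity-weighted comparison.

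- **Covariates the document supports:** baseline NYHA and MLHFQ (section 2.6.1), LVEF and cardiothoracic ratio (2.6.2), background drugs from the case report form (2.5), and history of myocardial infarction or revascularisation, which appears in the diagnostic criteria (2.3.1).
- **Covariates to confirm:** age, sex and comorbidities, if the case report form records them. The visit table is not shown, so this cannot be checked here.
- **Hospital:** use a random effect or grouping rather than 84 indicators. Sites average 1200/84 ≈ 14 patients, or 960/84 ≈ 11 after dropout.
- **Reporting:** show balance before and after adjustment, and keep the crude tests as descriptive.
- **Residual confounding:** add a sensitivity analysis for unmeasured confounding, such as an E-value. Dissatisfaction with western medication and its side effects are not documented as baseline items, so adjustment may not capture them fully.
- **Conclusion:** word it as an adjusted association.

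The change is mainly to the analysis text and needs no new data for the documented covariates. The cost is precision: power of about 0.76 to 0.65 if covariates explain 10% to 30% of exposure. Section 2.4 should say that its 0.80 power applies to the unadjusted comparison. Keeping 0.80 after adjustment would take about 1340 to 1724 patients on the same assumption.
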